### 9.2. Adverse events

An adverse event is any undesirable medical event occurring in the subject within the trial period, whether or not it is related to the study intervention. No serious adverse event has been reported of taking COVID-19 Rehabilitation Formula (CRF). The adverse reaction will be recorded and the treatment will be suspended when severe adverse reaction occurs. The assessment of adverse event will be recorded according to CTCAE 4.0 which is a standard assessment tool.

### 9.3. Serious adverse events

A serious adverse event is an adverse event that results in one of the following outcomes:

•Death.•Life-threatening.•In-patient hospitalization or prolongation of existing hospitalization.•A persistent or significant disability or incapacity.•A congenital anomaly or birth defect.

The definitions of causal relationship to study intervention are the same as those for adverse events. A standard serious adverse event form will be used (provided by The Joint Chinese University of Hong Kong---New Territories East Cluster Clinical Research Ethics Committee [Joint CUHK-NTEC CREC] at)^2^ to report the events within 24 h after acknowledgement.

## 10. Sample size and statistical methods

### 10.1. Sample size calculation

The primary outcome is Fatigue Severity Score (FSS). There is no any previous study on the Chinese medicine treatment of COVID-19 measured by FSS. The clinically meaningful improvement in FSS was assumed to be a drop of 9 out of 63 based on previous studies (33, 34). Based on the standard deviation of symptom score of residual fatigue in this study on COVID-19 recovered patients (33, 35), we assumed standard deviation estimates of 12. To detect a clinically meaningful difference of 9 points in FSS, sample size of 58 was estimated based on standard deviation estimates of 12 at an alpha of 0.05 and power of 0.8. It should be noted that these estimates are considered vague approximations, and 58 participants is a conservative estimate to detect a statistically significant result of change in FSS. To compensate a possible drop-out rate of 15%, totally 68 patients will be needed, with 34 in each group.

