## 4. Study outcomes

### 4.1. Primary outcome

Improvement of residual COVID-19 symptoms of fatigue using Fatigue Severity Score (FSS) at week 8.

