## 5. Study design

This is a double-blind, randomized, placebo-controlled superiority trial. Eligible subjects will receive either “CRF” granules or placebo granules for 8 weeks followed by a post-treatment visits at week 12.

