### 7.2. Baseline randomization visit

At randomization visit, eligible subjects will have medical consultation and assessment by registered Chinese medicine practitioners (CMPs) investigators. Vital sign will be assessed, medical history and concomitant medications will also be recorded. If the subject has a result of not detected or negative result of SARS-Cov-2 RT-PCR test of deep throat saliva/professional-administered combined nasal and throat swab, and negative medical and travel history related to COVID-19 within 72 h, subjects will be instructed to do a pulmonary function test using a designated spirometer and complete the questionnaires; however, performing deep throat saliva/professional-administered combined nasal and throat swab test and pulmonary function test are not mandatory. Subjects will be randomly assigned (in a 1:1 ratio) to receive 8 weeks of either “CRF” granules 23–42 g daily or placebo granules 23–42 g daily. CMP investigators will prescribe and dispense the study treatment accordingly.

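### The 58 evaluable patients are the bare minimum for 80% power, so calling that number conservative is unsupported, and the scale to which the SD of 12 applies is not stated

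*Protocol article*

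**What the plan says.** Section 5 sets the design: "This is a double-blind, randomized, placebo-controlled superiority trial". Randomisation is 1:1 (Section 7.2). The primary outcome in Section 4.1 is "Improvement of residual COVID-19 symptoms of fatigue using Fatigue Severity Score (FSS) at week 8".

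Section 10.1 builds the sample size in four steps:

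- The effect enters as a change over time: "The clinically meaningful improvement in FSS was assumed to be a drop of 9 out of 63".
- The SD of 12 is taken from a score: "Based on the standard deviation of symptom score of residual fatigue in this study on COVID-19 recovered patients".
- The same 9 points then become the target: "To detect a clinically meaningful difference of 9 points in FSS". With alpha 0.05 and power 0.8 this gives 58, raised to 68 (34 per arm) for 15% drop-out.
- The text concedes that the inputs are only rough, and in the same sentence adds that "58 participants is a conservative estimate to detect a statistically significant result of change in FSS".

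Section 10.2 makes tests two-sided. It compares groups by t-test or ANOVA, with covariates such as centre. It does not name baseline FSS as a covariate, and it does not say whether the between-arm test uses week-8 scores or changes from baseline.

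**The concern.** A sample size is conservative when it holds more patients than the planning inputs require, or when the inputs were deliberately set on the cautious side. Section 10.1 shows neither, and it describes the inputs as uncertain.

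Two shifts in wording add to the doubt. First, a drop of 9 is language for improvement within patients, whereas a placebo-controlled comparison needs the CRF-minus-placebo difference; no expected placebo response is given. Second, the SD is that of a score, while the closing sentence speaks of change in FSS. The SD of a change equals the SD of the score only at one particular correlation, and no correlation is given.

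What is at stake is how the result is read. A null result from a trial described as conservatively sized would be taken as firmer evidence against CRF than the design can support.

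**Working it through.** **Inputs.** Difference 9, SD 12, alpha 0.05, power 0.80, total 58 and drop-out 15% come from Section 10.1. Two-sided testing comes from Section 10.2, and 1:1 allocation from Section 7.2. The correlation r between baseline and week-8 FSS is not in the document, so the values below are assumptions.

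**1. Reproducing 58.** The standardised difference is 9/12 = 0.75. The normal approximation gives n per arm = 2(1.960 + 0.842)²/0.75² = 27.9, so 28 per arm and 56 in total. The two-sample t-test (noncentral t) gives 28.90, so 29 per arm and 58 in total, which matches the article. A one-sided t-test would need 23 per arm, and a one-sample or paired test 16 patients. The 58 is therefore a two-sided between-arm calculation, with 9 used as the difference between arms.

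**2. Margin.** Power by t-test is 78.7% with 28 per arm and 80.1% with 29. So 58 is the smallest even total that reaches 80%. For drop-out, 58/0.85 = 68.2 and 68 × 0.85 = 57.8 expected completers. The ten extra patients replace expected losses and add no reserve.

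**3. Sensitivity at 29 per arm (illustrative values).**

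| Difference | SD | Power |
|---|---|---|
| 9 | 12 | 80% |
| 9 | 13 | 74% |
| 9 | 11 | 87% |
| 8 | 12 | 70% |
| 7 | 12 | 59% |

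The row for a difference of 7 is what would follow if, for example, CRF patients dropped by 9 and placebo patients by 2 (9 − 2 = 7).

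**4. Score SD against change SD.** If 12 is the SD of the score at both visits, the SD of the unadjusted change is 12√(2(1 − r)), and the residual SD after adjustment for baseline is 12√(1 − r²). Power is for a 9-point difference with 29 per arm.

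| Assumed r | SD of change | Power, change | Residual SD, ANCOVA | Power, ANCOVA |
|---|---|---|---|---|
| 0.3 | 14.2 | 66% | 11.45 | 84% |
| 0.5 | 12.0 | 80% | 10.4 | 90% |
| 0.7 | 9.3 | 95% | 8.6 | 98% |

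Unadjusted change loses power against the stated 80% below r = 0.5 and gains above it. A comparison of raw week-8 scores has SD 12 and power 80.1% whatever r is. ANCOVA has a residual SD of at most 12. The ANCOVA powers ignore the one degree of freedom spent on the covariate.

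**The case against.** The strongest defence is that nothing has been miscalculated: 58 follows from the stated inputs. That stands.

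A reader might go further and infer that both inputs lean optimistic, that 80% is a best case, or that the trial is underpowered. The document supports none of these:

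- The score-versus-change question has no fixed direction. Power for unadjusted change could be well above 80%, and the primary outcome is tied to week 8, where a score SD may be exactly the right input.
- Reading 9 as a within-patient amount rests on the words of Section 10.1 alone, because the cited sources are not at hand. Choosing a clinically meaningful amount as the between-arm target is a legitimate design decision.
- The SD of 12 may have been rounded up from its sources, which could be what the article meant. That cannot be checked, and the text does not say so.
- Any trial planned at 80% loses power when its inputs are worsened. A full sensitivity table is commonly left to the complete protocol or analysis plan.

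It can also be said that the article already warns that its inputs are rough. That warning makes the label harder to defend: uncertain inputs call for a margin, and none was added. If nobody dropped out, 34 per arm would give 86%, but those patients are the declared drop-out allowance. The two patients between 56 and 58 separate the normal approximation from the t-test and are not a reserve.

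**Conclusion.** The point holds, and it is limited. Section 10.1 claims a property that its own figures do not show: 58 is the minimum for 80% power (80.1%) at a between-arm difference of 9 and SD 12, with no margin beyond drop-out. The section also leaves open whether the SD of 12 belongs to the score or to the change, and does not justify 9 as a CRF-minus-placebo difference.

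For unadjusted change, power at 58 runs from about 66% to 95% over assumed correlations of 0.3 to 0.7, so the effect of the ambiguity could go either way. The only shift with a clear direction is the one from drop to difference. It lowers power only if placebo patients improve and CRF patients drop by no more than 9, and the document gives no figure for the placebo response. The conclusion is that the description is unsupported and the analysed scale unclear. It is not that more patients are needed.

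**What to change.** 1. In Section 10.1, delete the word conservative. State that 58 gives 80% power for a CRF-minus-placebo difference of 9 points with SD 12 on the scale that is analysed, and say why 9 is the between-arm target. One sentence of illustration is enough: 74% at SD 13, and 59% at a difference of 7.
2. In Section 10.2, before unblinding, name the primary comparison as week-8 FSS by ANCOVA with baseline FSS as a covariate, alongside the centre term already foreseen. Table 1 schedules the questionnaires at day 0, so the covariate is already collected. This settles the choice between score and change. If the week-8 SD is 12, 58 patients then keep about 80% power or more for a 9-point difference (about 90% at r = 0.5).

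The cost is a less favourable description of the sample size and one added covariate. No more patients, visits or measurements are needed. If a fuller analysis plan already specifies this model, the article's section only has to agree with it.

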### 10.2. Statistical analysis

Baseline data (gender, age, and vital signs) will be descriptively summarized. Differences of measurement data between the groups will be assessed using *t*-test for normally distributed continuous variables and Wilcoxon signed rank test for non-normally distributed variables. Measurement data of different groups in each visit will be reported as mean ± standard deviation (SD). Intra-group comparisons between baseline and each visit will be conducted by using paired *t*-test (or Wilcoxon signed rank test). Comparisons between groups will be conducted by using an analysis of variance (ANOVA), with other confounding factors like multicenter character conducting the covariate analysis. Statistical analysis for the data which do not meet above conditions (e.g., non-normal) will be conducted with the use of non-parametric test. For laboratory parameters, Spearman’s coefficient correlation has been used for comparison with different parameters and one way ANOVA test for significant correlation between groups. Study flow chart and graphs will be presented over different study times.

All *p*-values and 95 percent confidence intervals are two-sided, and *p* < 0.05 is considered statistically significant. Statistical analyses will be carried out exclusively by an independent statistician. All analyses will be performed by using SPSS, version 24 (SPSS).

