**Methods:**

Eligible subjects will be randomly divided into treatment group and control group in 1:1 ratio. Treatment group will receive CRF along with certain pre-defined CM according to symptoms for 8 weeks, while control group will receive equivalent packs of placebo for 8 weeks. Data in terms of Fatigue Severity Score (FSS), self-reported COVID-19 long term symptom assessment, the modified British Medical Research Council (mMRC) Dyspnoea Scale, EuroQol Five-Dimension Five-Level (EQ-5D-5L) Questionnaire, pulmonary function test and adverse events will be collected and analyzed by SPSS 24. Blood test on liver and renal functions will also be conducted as safety measures.

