#### 7.4.3. The modified British medical research council (mMRC) dyspnoea scale

The mMRC scale is a five-category scale to characterize the level of dyspnoea with physical activity in which higher scores correspond with increased dyspnoea (6).

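### Section 10.2 names the Wilcoxon signed rank test, a paired test, for non-normal differences between two independent randomised arms

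*Protocol article*

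**What the plan says.** The design is a two-arm parallel trial. Section 5 states: "This is a double-blind, randomized, placebo-controlled superiority trial". The Methods part of the abstract adds: "Eligible subjects will be randomly divided into treatment group and control group in 1:1 ratio". No matching of patients and no crossover is described.

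Section 10.2 of the protocol article contains four rules that bear on this point:

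- **Between groups, first rule.** "Differences of measurement data between the groups will be assessed using" the t-test where the variable is normal, and the "Wilcoxon signed rank test for non-normally distributed variables".
- **Within groups.** "Intra-group comparisons between baseline and each visit will be conducted by using paired" t-test, with the signed rank test as the bracketed alternative.
- **Between groups, second rule.** "Comparisons between groups will be conducted by using an analysis of variance (ANOVA"), with covariates such as centre.
- **Fallback.** Data that do not meet these conditions ("e.g., non-normal) will be conducted with the use of non-parametric test"), with no test named.

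Neither the rank-sum test nor the Mann-Whitney test is named anywhere in the article.

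**The concern.** The signed rank test works on differences within pairs. It suits a patient's change from baseline, which is how the within-group sentence uses it. It does not suit a comparison of one set of patients with a different, unmatched set.

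An analyst who follows the between-group sentence literally has three options, none of them satisfactory. If the arms end with unequal numbers, the test cannot be run. If the numbers are equal, patients must be paired by something arbitrary such as row order, and the p-value then depends on that order. Or the test is run on change within each arm, and the randomised comparison is lost.

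The non-normal branch is not remote. The mMRC is a "five-category scale to characterize the level of dyspnoea with physical activity", and the symptom assessment in section 7.4.2 also has five levels. A superiority trial should not leave the choice of a workable test to be made once the data are in hand.

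**Working it through.** **1. Can the sentence be read as a within-arm rule?** No. It speaks of differences between the groups and sets the signed rank test beside the plain t-test. Within-arm comparisons have their own sentence, with the paired t-test.

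**2. Does the plan elsewhere treat the arms as independent?** Yes; its sample size does. Inputs from section 10.1: difference 9, SD 12, alpha 0.05 (two-sided by section 10.2), power 0.80.

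- Normal approximation: n per arm = 2 × (1.960 + 0.842)² × 12² / 9² = 27.9, so 28 per arm, 56 in total.
- Two-sample t-test (noncentral t): 28.9, so 29 per arm and 58 in total. This is the plan's figure; power at 29 per arm is 0.801.
- Paired t-test with standardised effect 9/12 = 0.75: about 16 pairs. This does not give 58.

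**3. How likely are equal arms at week 8?** Section 10.1 plans 34 per arm and 15% drop-out. Assume that patients drop out independently at that rate in both arms. The number of completers per arm then has variance 34 × 0.85 × 0.15 = 4.335. The chance of equal numbers is about 1 / (2 × √(π × 4.335)) = 0.14, and the exact binomial sum is also 0.14. Unequal arms would therefore occur in about 86% of such trials. With 28 against 29 values, the paired differences do not exist and the routine stops with an error.

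**4. If the arms are equal, what does arbitrary pairing do?** Two illustrative data sets of 29 per arm, each with a rank-sum p-value a little below 0.05, had one arm re-ordered at random 2,000 times.

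| Data set | Rank-sum p | Signed rank p over re-pairings |
|---|---|---|
| A (observed mean difference 6.5, normal, SD 12) | 0.033 | 0.002 to 0.16 (full range); 0.014 to 0.088 (5th to 95th percentile) |
| B (FSS-like scores, limited to 9–63) | 0.028 | 0.008 to 0.085 (2.5th to 97.5th percentile); 77.5% below 0.05 |

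The rank-sum test gives one p-value per data set. The signed rank test falls on either side of 0.05 according to row order.

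**5. Error rates over repeated trials.** Simulation with 29 per arm, SD 12 and 4,000 runs per row; the skewed case is a gamma distribution with shape 2, scaled to SD 12.

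| Data | True difference | Signed rank, arbitrary pairing | Mann-Whitney | Tests disagree at 0.05 |
|---|---|---|---|---|
| Normal | 0 | 0.042 | 0.041 | 0.026 |
| Normal | 9 | 0.77 | 0.77 | 0.072 |
| Skewed | 0 | 0.050 | 0.052 | 0.030 |
| Skewed | 9 | 0.82 | 0.89 | 0.090 |

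Type I error stays near nominal. With skewed data about 7 percentage points of power are lost (0.89 − 0.82).

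**6. Will FSS, the primary outcome, reach this branch?** The article gives no expected FSS mean and names no normality check, so both must be assumed. With SD 12, scores clipped to 9–63 and n = 58, a Shapiro-Wilk test rejects normality in about 4% of trials at mean 36, 6% at mean 40, 28–29% at mean 45 and 90% at mean 50. For change scores (assumed correlation 0.5, mean drop 4.5) it rejects in about 5–6.5%, close to the nominal rate. The answer depends on assumptions that the documents do not settle.

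**The case against.** The strongest reply is that section 10.2 has a second between-group rule. It uses ANOVA and sends data that fail its conditions to an unspecified non-parametric test, and a rank-sum test fits that wording. This stands in part. A reader might infer that every non-normal between-arm comparison is tied to the signed rank test; the fallback shows that this goes too far. But the fallback names nothing, the only non-parametric test named for group differences is the wrong one, and the first sentence remains uncorrected.

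A second reply is that the harm is small. The sample size treats the arms as independent, so the wording is probably a slip for rank-sum, and with unequal arms the independent statistician would meet the problem at once. That is plausible, and silent pairing by row order is not the likeliest outcome. It is still better to choose the replacement test before the data are seen.

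A third reply is that calling the test invalid suggests false positives. A reader might infer inflated type I error; the simulations do not show it. The fault is that the test does not apply to this comparison and depends on row order.

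Finally, an analysis plan that is not shown may name the right test. That would not clear the article: it does not leave the test open but states one, and an analysis plan with the right test would contradict it.

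**Conclusion.** Wrong as written. The article assigns a paired test to a comparison of independent arms and names the appropriate test nowhere. This rests on the text alone.

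The size is limited. The rule is not computable with unequal arms (about 86% of trials if drop-out is independent at 15%), depends on row order with equal arms, and costs about 7 points of power in the one skewed distribution examined and essentially none with normal data. The two re-pairing examples lie close to the 0.05 threshold and illustrate the problem; they do not measure how often it would change a conclusion.

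The point bears most on the mMRC and symptom scales, where five ordered levels make normality implausible. It would be tempting to say that the primary FSS analysis will fall into this branch, but the documents do not support a prediction: it depends on the FSS mean and on whether the score or its change is analysed. Outcomes analysed by t-test or ANOVA are unaffected.

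**What to change.** In section 10.2, and in the analysis plan if it repeats the wording:

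1. In the between-group sentence, replace the signed rank test with the Wilcoxon rank-sum (Mann-Whitney U) test.
2. In the later fallback sentence, name the same test for between-group comparisons.
3. Keep the signed rank test for within-arm change from baseline only.

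The cost is a change of wording in two sentences, made before unblinding; the test is available in SPSS. No stated figure changes, because 58 and 68 come from the two-sample t-test. For information only: if the rank-sum test became the main FSS test, the 28 per arm of the normal approximation would become 28/0.955 = 29.3, so 30, under normality, and at most 28/0.864 = 32.4, so 33, for a pure location shift. Both are below the 34 randomised per arm, though above the 29 evaluable.

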## 2. Hypothesis

The residual symptoms of COVID-19 recovered patients can be improved after taking Chinese medicine.

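### No single primary analysis is designated for week-8 FSS: the between-arm tests overlap, baseline adjustment is not specified, and score versus change is undefined

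*Protocol article*

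**What the plan says.** Section 4.1 gives the primary outcome as "Improvement of residual COVID-19 symptoms of fatigue using Fatigue Severity Score (FSS) at week 8". Section 10.1 sizes the trial on a between-group difference: "To detect a clinically meaningful difference of 9 points in FSS, sample size of 58 was estimated", with "standard deviation estimates of 12 at an alpha of 0.05 and power of 0.8". The next sentence of 10.1 describes the 58 as enough for a significant result on change in FSS. Section 10.2 makes all tests and intervals two-sided.

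Section 10.2 then gives several rules for comparing the arms:

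- a t-test for normally distributed measurements, and a Wilcoxon signed rank test otherwise;
- "Comparisons between groups will be conducted by using an analysis of variance (ANOVA), with other confounding factors like multicenter character conducting the covariate analysis";
- as a fallback, some non-parametric method, not named, wherever the data fail the earlier assumptions, with non-normality given as the example.

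Separately, 10.2 plans within-arm comparisons of each visit with baseline by paired t-test or signed rank test. Questionnaires are completed at the baseline visit (section 7.2 and Table 1), so baseline FSS is available. Section 5 calls the study a placebo-controlled superiority trial. Section 2 states the hypothesis without a comparator: "The residual symptoms of COVID-19 recovered patients can be improved after taking Chinese medicine".

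**The concern.** A confirmatory trial needs one stated analysis of its primary endpoint. Here three choices are left open at once:

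1. **Scale.** Week-8 score, or change from baseline.
2. **Adjustment.** Unadjusted, or adjusted for an open list of covariates of which only centre is named.
3. **Test family.** Parametric or rank-based, decided from the observed data with no stated criterion.

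Different combinations give different p-values for the same endpoint, and nothing in the article says which one counts.

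The rank-based branch also has an error. The signed rank test works on paired differences within one sample, so it cannot compare two independent arms. The two-sample form is the rank-sum test.

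Baseline FSS is likely to be a strong predictor of week-8 FSS and is already being collected. Leaving it unnamed as a covariate gives up precision in a trial with about 29 evaluable patients per arm. Its only explicit use in 10.2 is in the within-arm tests. Those tests mix treatment effect with natural recovery and regression to the mean, so they do not answer the superiority question in section 5.

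**Working it through.** **Inputs.** From section 10.1: difference 9, SD 12, alpha 0.05, power 0.80, 58 evaluable, 15% dropout, 68 in total. From 10.2: two-sided. From the abstract: 1:1 allocation. The correlation r between baseline and week-8 FSS is not in the article; I assume 0.3 to 0.7, with equal SDs at the two visits.

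**The plan's own figure.** The standardised difference is 9/12 = 0.75. The exact two-sample t-test needs 28.9 per arm for 80% power, so 29 per arm and 58 in total. Power at 29 per arm is 80.1%. Allowing for dropout, 58/0.85 = 68.2, against 68 stated. The 58 is therefore what an unadjusted two-sample t-test requires.

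**Effect of scale and adjustment.** Let s be the SD of the score.

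- Week-8 score, unadjusted: SD = s
- Change score, unadjusted: SD = s × √(2(1 − r))
- ANCOVA on baseline: residual SD = s × √(1 − r²)

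Since 1 − r² is at most 1, and 1 − r² = (1 − r)(1 + r) is at most 2(1 − r), the ANCOVA SD is never the largest of the three, whatever r is. Section 10.1 does not say whether 12 is the SD of the score or of the change, so both readings are worked. Power is for difference 9 and 29 per arm, by exact two-sample t. This ignores the one degree of freedom spent on baseline and the few spent on site.

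*Reading A: 12 is the SD of the week-8 score (s = 12).*

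| r | Week-8 score | Change: SD, power | ANCOVA: SD, power |
|---|---|---|---|
| 0.3 | 80% | 14.20, 66% | 11.45, 84% |
| 0.5 | 80% | 12.00, 80% | 10.39, 90% |
| 0.6 | 80% | 10.73, 88% | 9.60, 94% |
| 0.7 | 80% | 9.30, 95% | 8.57, 98% |

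*Reading B: 12 is the SD of change, so s = 12/√(2(1 − r)).*

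| r | Change | Week-8 score: SD, power | ANCOVA: SD, power |
|---|---|---|---|
| 0.3 | 80% | 10.14, 91% | 9.67, 94% |
| 0.5 | 80% | 12.00, 80% | 10.39, 90% |
| 0.6 | 80% | 13.42, 71% | 10.73, 88% |
| 0.7 | 80% | 15.49, 58.5% | 11.06, 86% |

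As long as the scale of analysis matches the scale of the SD, the plan keeps its 80%. If they differ, power can fall to 66% (reading A, r = 0.3) or 58.5% (reading B, r = 0.7). ANCOVA stays above 80% in every row of both tables.

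**Effect of an open choice of test.** In 20,000 simulated trials per value of r (0.3, 0.5, 0.7), with no treatment effect, normal data and 29 per arm, the smallest available p-value fell below 0.05 in:

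- 5.6% to 5.9% of trials, choosing between t-test and rank-sum test on the week-8 score;
- 8.4% to 9.4%, choosing between a t-test on the week-8 score and one on change;
- 9.9% to 11.1%, choosing among all four (t or rank-sum, score or change).

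These are ceilings, reached only if the most favourable result were always taken. Most of the excess comes from score versus change, and little from t-test versus rank test.

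**The case against.** The strongest reply is that this is a condensed article. Covariates and model details usually sit in the analysis plan, which is not shown. That is fair for detail that is merely absent. It does not cover what 10.2 itself lays down: overlapping rules, a switch of test driven by the data, and a paired test for independent arms.

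The reply does defeat several stronger readings:

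- **That the plan ignores baseline FSS.** Improvement in 4.1 and change in 10.1 both allow a change score, which uses baseline by subtraction, and centre is given only as an example of a covariate. What can be said is that baseline adjustment is not specified and the scale is undefined.
- **That the t-test and the ANOVA are rival results.** With two arms, an unadjusted ANOVA is the t-test (F = t²). The t-test sentence also follows the sentence on baseline data and might concern baseline comparability only. The adjusted-versus-unadjusted choice and the non-parametric switch remain on that reading too.
- **That the trial is underpowered.** It reaches 80% on its own inputs. The loss is relative to ANCOVA, and its size depends on an assumed correlation.
- **That chance baseline imbalance biases the result.** An unadjusted randomised comparison is unbiased, and its standard error already allows for such imbalance. The cost is precision.
- **That efficacy will be claimed from within-arm tests.** The article never says so; it lists between-arm comparisons separately and declares a superiority design. How often such tests would mislead depends on the natural recovery in FSS, which the article does not give, so I put no figure on it.

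**Conclusion.** The point stands as one of specification, and the plan should be changed. Section 10.2 fixes no single primary analysis of week-8 FSS, names an invalid test for the non-normal branch, lets the data choose the test family, and does not name baseline FSS as a covariate. Sections 4.1 and 10.1 leave the scale open. These statements rest on the text alone.

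The size is conditional. It assumes a correlation of 0.3 to 0.7, equal SDs at both visits and 29 evaluable per arm. Compared with the planned 80%, ANCOVA gains about 4 to 18 percentage points under reading A (84% to 98%) and 14 down to 6 points under reading B (94% to 86%). The downside of the undefined scale is an unadjusted analysis at 66% or 58.5% in the least favourable cases examined. A reader should not infer that the sample size is wrong or that error inflation will occur; the article supports neither.

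**What to change.** In section 10.2, or in the analysis plan before unblinding:

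1. Name one primary analysis: week-8 FSS by ANCOVA with arm, baseline FSS and site, reporting the adjusted between-arm difference with its 95% CI whatever any normality check shows.
2. Make a two-sample rank-based analysis (rank-sum, not signed rank) a sensitivity analysis only.
3. Use the same model for week-12 FSS and EQ-VAS.
4. Report within-arm changes descriptively, and state that the efficacy conclusion rests on the between-arm comparison, as the superiority design in section 5 requires.
5. Align 4.1 and 10.1 with this analysis, and say whether the SD of 12 refers to the score or to the change.

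The cost is wording only. Baseline FSS is already collected, and no visit, measurement or patient is added.
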